### Implementation phase

Assess the effectiveness of the HOPE 2.0 intervention and the success of the implementation plan in a hybrid type 2 trial.

*Hypothesis: Cervical screening uptake by HPVSS will be significantly higher among WLWH in the intervention vs. the control group, and implementation outcomes scores among intervention group providers will be significantly higher than those of control group providers.*

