#### Sample size estimation

The sample size is calculated based on implementation outcomes of health system adoption, cost, fidelity, penetration, and sustainability.*For power calculation*, we used Power (1 − β) = 0.8 and α = 0.05 and did not assume equal cluster sizes. The coefficient of variation (CV) of cluster sizes is set to 0.2, allowing for a large variability between clusters. Methods from Donner et al. [59] implemented in R for cluster RCTs were used.*For binary outcomes**,* e.g., adoption, we assumed 15% adoption in the control group based on previous study [23]. Table 3 shows the sample size needed to detect increases in implementation outcomes (e.g., adoption) in the intervention arm from 15% to 25–50% with 80% power. We expect to achieve an increase of at least 15%, to 30% or more, for outcomes such as adoption.*For continuous outcomes* such as sustainability/sustainment, we used estimated variance = 1 (standardized), and variance within clusters = 0.95 (assuming a large proportion of individual WLWH variability). For average cluster sizes (sampling frame per facility) ranging from 400 to 600 WLWH, we have greater than 80% power to detect differences in mean scores between the intervention and control arms as small as 1.4. We aim to recruit at least 1,152 patients (288 per site × 4 sites, inclusive of 20% attrition for a minimum sample size of 240 per site) Thus, the sample size for the Intervention Arm is *n* = 576 and Control Arm is *n* = 576.

**Table 3 Tab3:** Power and sample size calculation

Intervention Numeric	Control Numeric	Minimum Sample Size Per Site
0.25	0.15	504
0.30	0.15	240
0.35	0.15	142
0.40	0.15	94
0.45	0.15	67
0.50	0.15	50

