### Randomization

Study sites are the unit of randomization, and all providers and WLWH at a given HIV clinic at each site will be randomized to the same study arm. Using computer-generated numbers with a block of 2, the four study sites will be randomized to one of two arms: two sites in the intervention group and two sites in the control group (Fig. 3).

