### Statistical analysis plan

Data will be cleaned and reviewed to determine if distributional assumptions are met. If not, scores will be transformed, or appropriate nonparametric methods will be applied. If distributional assumptions are valid, sensitivity analyses (with and without outliers) will be applied. Hypothesis testing will use α = 0.05 (2-tailed). An intent-to-treat analysis will be used to maintain baseline comparability achieved by randomization.

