#### Quantitative data analysis

Descriptive analysis will be used for implementation outcomes scores at each health facility; scores will be compared within health facilities and between study arms over time. Mixed models (Linear Mixed Models or Generalized Linear Mixed Models) will account for repeated participant measures.*For Likert scale items (surveys)*, we will use ANOVA to determine differences in implementation outcome scores between study arms, with Tukey HSD (honestly significant difference) post hoc analysis to determine specific sites that significantly differ.*For continuous outcome variables*, we will similarly use linear mixed models to analyze treatment effects while controlling covariates, including age, education, income, religion, marital status, employment, insurance, and clinical conditions consistent with our previous studies [68, 69].*Fidelity analysis:* The fidelity checklist and activity log sheets at each study site will be aggregated, and composite site scores will be calculated and compared across intervention and control sites.*Cost-Effectiveness Analysis:* Costs will be determined using the cost trackers described. At the facility level, we will use the WHO Incremental Cost-Effectiveness Ratio (ICER) [70]. A formula to analyze the cost-effectiveness outcome, whose outcome of interest is screening and treatment. An ICER is calculated by dividing the difference in total costs (incremental cost) by the difference in the chosen measure of health outcome or effect (incremental effect) to provide a ratio of ‘extra cost per extra unit of health effect. We will determine the Total Cost [average fixed and variable costs (TC)] for screening and treatment in IG (Arm 1) and CG (Arm 2), and cervical cancer cases averted (incremental effect) for each Arm. Then ICER = Incremental cost/Incremental effect. An ICER of less than 1 indicates that the control group is cost-effective, an ICER greater than 1 suggests the intervention group is cost-effective, and an ICER equal to 1 indicates a similar cost for both arms. At the patient level, we will calculate the average cost per patient in both arms.

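### The sample size is said to cover fidelity, but fidelity is compared as composite site scores, two sites against two, and the number of women enrolled does not power that comparison

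*Protocol article*

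**What the plan says.** - **Sample size estimation:** "The sample size is calculated based on implementation outcomes of health system adoption, cost, fidelity, penetration, and sustainability". For the calculation, "we used Power (1 − β) = 0.8 and α = 0.05". The result is a number of women: at least 240 per site, raised by 20% to 288, over four sites (1,152). The worked figures are for binary outcomes, with adoption as the example, and for continuous outcomes, with sustainability as the example. None is given for fidelity.
- **Randomization:** "two sites in the intervention group and two sites in the control group".
- **Quantitative data analysis, fidelity item:** checklists and activity logs are aggregated by site, and "composite site scores will be calculated and compared across intervention and control sites". No test is named.
- **Statistical analysis plan:** one general rule covers testing ("Hypothesis testing will use α = 0.05 (2-tailed"). If distributional assumptions fail, "scores will be transformed, or appropriate nonparametric methods will be applied". Site-level scores are not exempted.
- **Implementation phase, hypothesis:** "implementation outcomes scores among intervention group providers will be significantly higher than those of control group providers".
- **Outcomes measures:** fidelity is a secondary outcome.

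**The concern.** The unit in the sample size statement and the unit in the fidelity analysis do not match. The first counts women. The second compares four numbers, one per site, built from checklists and logs. More women per site cannot turn four site scores into more than four.

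Fidelity matters for reading this trial. The arms differ mainly in the implementation support given to providers, and whether that support improved delivery is part of the explanation for any difference in uptake. If the four composites were tested and gave a non-significant result, a reader of the sample size section could believe the comparison had 80% power and take the result as evidence that the support does not improve fidelity. The design could not support that conclusion.

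**Working it through.** **Inputs.** Two sites per arm (Randomization). Two-sided alpha 0.05 (Statistical analysis plan). Power 0.80, total variance 1, within-cluster variance 0.95 and cluster-size CV 0.2 (Sample size estimation). The SD of the composite fidelity scores is not given, so results are in units of that SD.

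**1. The plan's own continuous figure.** The variance split implies an intracluster correlation of 1 − 0.95 = 0.05. With m women per site:

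- Design effect = 1 + ((CV² + 1)m − 1) × 0.05. For m = 400 this is 1 + (416 − 1) × 0.05 = 21.75; for m = 600 it is 32.15.
- SE of the arm difference with two sites per arm = √(2 × DE / 2m) = √(DE/m). This is √(21.75/400) = 0.233 for m = 400 and √(32.15/600) = 0.232 for m = 600.
- On a t-test with 2 df, power at a difference of 1.4 is 0.836 to 0.840. At 1.3 it is 0.791 to 0.796.

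So 1.4 is the smallest difference, to one decimal, with more than 80% power. The stated figure reproduces for woman-level means. It still holds at 240 or 288 women per site (power 0.828 and 0.831). It is 1.4/0.233 = 6.0 standard errors, so the plan's own figure already carries the cost of 2 df.

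**2. A t-test on four fidelity composites.** Let σ be the SD of a site score.

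- SE of the arm difference = σ√(1/2 + 1/2) = σ.
- Degrees of freedom = 2 + 2 − 2 = 2; the two-sided 0.05 critical value is 4.303.
- The noncentrality is therefore the true difference divided by σ.

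| True difference (site SDs) | Power |
|---|---|
| 1 | 0.095 |
| 2 | 0.218 |
| 3 | 0.387 |
| 4 | 0.565 |
| 5 | 0.719 |
| 5.7 | 0.805 |

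Power reaches 80% at 5.65 site SDs. A simulation of 1,000,000 trials at that value gave 0.7998. The number of women per site appears in none of these expressions.

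**3. A rank or permutation test.** Four scores can be split two against two in C(4,2) = 6 ways. With complete separation, the observed split and its mirror image are the most extreme, so the smallest exact two-sided p is 2/6 = 0.333. Large-sample p-values do not reach 0.05 either: the minimum is 0.121 for Kruskal-Wallis or an uncorrected Mann-Whitney test. An exact two-sided rank test gives at best 2/20 = 0.10 with three sites per arm, and first gets below 0.05 with four (2/70 = 0.029).

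**The case against.** The strongest reply is that no significance test on the composites is written. The Quantitative data analysis section names its tests where it wants them (ANOVA with Tukey comparisons, linear mixed models). It opens by describing implementation scores descriptively, and for fidelity it says only that the site scores are compared. A descriptive reading is natural, and naming a test is a detail an article may leave to the full analysis plan. This stands, and it is why the point is conditional on a test being made. It does not rescue the sample size statement, which claims coverage of fidelity whichever reading is taken.

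Further replies also carry weight:

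- The hypothesis concerns provider scores, and fidelity is also collected from providers by survey, so the composite is not the only fidelity measure. This is correct. Those data remain clustered in four sites, but that is a separate matter.
- The fallback offers transformation as an alternative and names no method; it says only that "appropriate nonparametric methods will be applied". The plan is not committed to a rank test.
- The figure of 5.7 SDs looks extreme partly because of its unit. Under the plan's variance split the between-site SD is √0.05 = 0.22, and the plan's 1.4 is itself 1.4/0.22, about 6.3 of these. This is fair.
- No power figure specific to fidelity is printed, so a misreading of a null result is a risk and not something the article states.

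Two stronger readings are tempting. A reader might infer that a non-significant fidelity result is nearly assured. The t-test figures do not support this, since power passes one half by 4 site SDs and the size of σ is unknown. A reader might also convert the result to score units by treating each composite as an average over the site's providers with the plan's variance split, or raise the minimum p by permuting within randomization blocks. The documents do not say that the composite is a provider mean, the 0.95 is justified by variability among women, and no block-restricted test is planned.

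**Conclusion.** The point holds in limited form. The sample size statement includes an outcome that the number of women enrolled does not power, and the general testing rule does not exempt site-level scores. If the composites are tested, the t-test needs about 5.7 site SDs for 80% power. At 2 and 3 site SDs the chance of a non-significant result is 78% and 61%. Under an exact rank or permutation test it is certain, because p cannot fall below 0.33.

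These figures assume one composite per site, two sites per arm, independent and roughly normal site scores with equal variance for the t-test, and two-sided alpha 0.05. They do not assume a value for the site SD. The outcome is secondary and the remedy is wording. The plan's 1.4 for woman-level means is not in question.

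**What to change.** **Sample size estimation.** Remove fidelity from the outcomes the sample size is said to cover. Alternatively, keep it and state that, for composite site scores with two sites per arm, the detectable difference at 80% power and two-sided alpha 0.05 is about 5.7 SDs of the site scores.

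**Quantitative data analysis, fidelity item.** State that the composite scores are reported descriptively, as the four site values and the difference between arm means. If an interval is wanted, use a t-based 95% interval on 2 df; its half-width is 4.303 times the pooled site SD. That interval carries the same information as the t-test, so it should be presented as a display of imprecision. Add that no rank-based test is applied to site-level scores, which also settles how the general nonparametric fallback applies to them, and that a null result is not read as evidence of no effect on fidelity.

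**Cost.** Wording only, with no extra data, sites or participants. The sponsor gives up a power claim for a secondary outcome.

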### Outcomes measures

The primary outcomes of interest in this type 2 hybrid trial are 1) the effectiveness of the HOPE 2.0 intervention in increasing uptake of cervical screening among WLWH, and 2) the adoption of HOPE 2.0 intervention at the facility level. Other outcomes, including cost, fidelity, penetration, and sustainability, will be assessed as secondary outcomes. Additionally, Proctor et al.’s [61] client (i.e., WLWH) health outcomes will also be assessed (Fig. 2).*Cervical screening uptake* is defined as the proportion of WLWH in each study arm that successfully complete the cervical screening process. In the intervention arm, completing the process requires the WLWH to present to the clinic, collect a self-test kit, collect a cervical sample, and submit the sample to the clinic for testing. In the control arm, completing the process requires the WLWH to present to the clinic and receive a pap smear/cervical sample collection from a provider. WLWH in either study arm who do not complete the entire process will not be considered as completing uptake. Uptake assessment will therefore be determined as proportion of WLWH with complete screening out of all women enrolled in each study arm.*Program Adoption* is defined as the decision of healthcare workers (i.e., providers and management) and patients (described as patient uptake) to commit to and use HOPE 2.0 and ISS adoption. Adoption will be measured at provider, management, and patient levels using a variety of data logs, surveys, and interviews.At the management level, we will assess (i) the number of ISS training sessions attended and (ii) the degree to which ISS components are used to support providers.At the provider level, we will assess (i) the number of ISS training sessions attended, (ii) the degree to which ISS components are used, and (iii) the number of implementation plan steps followed. Additionally, we will assess providers’ (i) implementation experience (i.e., resource availability, managerial support, and technical issues confronted); and (ii) operational experience (i.e., workload increase or decrease, flow of health facility communication, and any skills needed).*Implementation Cost* is defined as the total expenses (facility/provider and patient) for implementing HOPE 2.0. Cost will be assessed at the health facility level in both study arms. We will use a micro-costing approach to estimate the economic costs associated with each study arm. The direct measure method of micro-costing involves tracking resources used and enumerating unit costs for each resource to precisely estimate cumulative costs associated with each study arm [62]. Implementation cost will be measured at the health facility level and patient level, utilizing a variety of cost-tracking databases throughout the study period to itemize, quantify, and value resources.At the health facility level, a cost-tracking database will be used throughout the study period to itemize, quantify, and value resources. Costs at the facility level include (i) number of hours staff spent on HOPE 2.0 training; (ii) sampling materials, including kits and laboratory testing costs; (iii) recruitment (i.e., time spent identifying and contacting eligible women, advertising materials, participant incentives); (iv) HOPE 2.0 delivery (with and without ISS); and (v) treatment and biopsies.Cost to the patient will include tracking of participant out-of-pocket costs (e.g., transportation, childcare, phone data, time spent on HOPE 2.0 procedures). French et al.’s outpatient cost survey [63] (5 items) will be adapted to measure patient-level costs.Note: Time effort will be estimated using the hourly wages of WLWH and healthcare workers.*Fidelity* is the degree to which HOPE 2.0 and its ISS are implemented as planned.At the provider level, utilizing surveys, log sheets, and interviews, we will assess (i) the degree of adherence to HOPE 2.0/ISS protocols (Intervention) and HOPE 2.0 (Control) during implementation, (ii) the dose of the program delivered, and (iii) the quality of program delivery.At the management level, we will assess (i) adherence to ISS protocol (Intervention only) and (ii) overall management support for providers (both arms).We will utilize log sheets and interviews, as well as observations, and the Process Evaluation Checklist (PEC) [64] throughout to track the fidelity of implementation and overall project progress.*Program Penetration* for this proposal is the integration of HOPE 2.0/ISS within the HIV subsystem of study facility settings [61]. We will assess penetration outcomes at provider and management levels by determining the proportion of personnel who actually deliver on a HOPE 2.0 program task/role, out of the number trained or expected to deliver on that task/role.At the management level, we will utilize log sheets and interviews to measure the expected tasks or roles to be evaluated, which will be (i) the provision of technical support and (ii) facilitating a conducive HOPE 2.0 implementation climate for providers.At the provider level, we will utilize log sheets and interviews to measure the expected tasks to be evaluated, which are (i) screening and recruitment of eligible WLWH, (ii) delivery of HOPE 2.0 to enrolled WLWH, and (iii) follow-up on all testing outcomes and completion of required documentation for these tasks/roles.*Program Effectiveness* is defined as the impact of the ISS on 1) providers' self-efficacy in implementing HOPE 2.0, 2) WLWH screening uptake, and 3) treatment outcome. We will assess effectiveness outcomes at management, provider, and WLWH levels utilizing surveys, log sheets, and interviews.At the management level, we will assess (i) the frequency of support that management delivers to providers, (ii) management self-efficacy in supporting HOPE 2.0 implementation, and (iii) challenges in supporting HOPE 2.0 implementation at their facilities, utilizing log sheets and interviews.At the provider level, we will assess (i) self-efficacy for implementing HOPE, (ii) fidelity of HOPE 2.0 intervention delivery, (iii) number of WLWH screened and women with positive results who are treated, and (iv) the type, frequency, duration, and quality of service provided to patients (WLWH).At the WLWH level, we will assess the impact of HOPE 2.0 on patients’ (WLWH) screening uptake (i.e., service outcome) and receipt of screening results, patient satisfaction, and for women with positive screening results, clinical follow-up, and evaluation for, and receipt of CC treatment where appropriate (i.e., client outcomes). Assessment procedures: WLWH in both study arms will complete the screening and satisfaction outcome survey within one month of completing HOPE 2.0. Within one month of screening, providers will check the lab registry and will review the electronic medical record to confirm screening completion. Treatment compliance will be evaluated within 6 months of positive result notification. The screening and treatment completion outcomes will be binary (yes/no), test results (positive, negative, or inadequate), treatment follow-up (yes, no, or lost-to-follow-up), and patient satisfaction will be measured using a patient satisfaction survey [65].

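### The cost-effectiveness analysis names two different effect measures, and the one in the ICER denominator, cervical cancer cases averted, cannot be obtained from the data the trial records

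*Protocol article*

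**What the plan says.** The Protocol article, Quantitative data analysis, sets out the cost-effectiveness analysis in one paragraph. It introduces the ICER as follows: "A formula to analyze the cost-effectiveness outcome, whose outcome of interest is screening and treatment". It then explains the ICER in general terms as a difference in total cost over a difference in effect. Next it says that total cost will be determined in each arm, together with "cervical cancer cases averted (incremental effect) for each Arm". It closes the definition with "Then ICER = Incremental cost/Incremental effect".

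Other sections bear on whether that denominator is available:

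- **Outcomes measures** lists what is recorded on the women: "The screening and treatment completion outcomes will be binary (yes/no), test results (positive, negative, or inadequate", then treatment follow-up and satisfaction. Treatment compliance is evaluated within 6 months of notification of a positive result. Cancer incidence is not listed.
- **Sustainment phase, Study population** runs to 18 or 24 months, but its measures are taken on providers, managers and policymakers.
- **Implementation phase, Design** gives HOPE to the control arm as well. Outcomes measures instead describes control-arm uptake as a Pap smear or provider-collected sample. The two should be reconciled, but on either account controls are offered screening.
- **Sample size estimation** fixes the size: "sample size for the Intervention Arm is *n* = 576 and Control Arm is *n* = 576".

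**The concern.** An ICER is only as good as its denominator, and here one paragraph gives two. Screening and treatment are observed in the trial. Cases averted are not: that quantity compares what happened with what would have happened otherwise, and the benefit of treating a precancerous lesion falls after the women's follow-up ends. The paragraph sets the effect beside tracked costs, arm by arm, and gives no step from one measure to the other.

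An analyst following the text therefore has either no value to enter or a temptation to count cancers that come to light. Such a count would mislead. Cancers found through screening or biopsy are cases detected, not averted, and the arm that screens more women may find more of them. The sign of the effect could then reverse. What is at stake is the interpretability of the cost-effectiveness result.

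**Working it through.** **1. Which measure is available?**

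| Effect named in the paragraph | Recorded on the women? | Between-arm difference obtainable? |
|---|---|---|
| Screening completed | Yes, binary | Yes |
| Treatment completed after a positive screen | Yes, within 6 months of the result | Yes |
| Cervical cancer cases averted | No; no incidence outcome, no model stated | Not from trial data |

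This comparison alone carries the point. The arithmetic below only illustrates what a within-trial count would look like.

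**2. Arm size (Sample size estimation).** The text says "at least 1,152 patients (288 per site × 4 sites, inclusive of 20% attrition for a minimum sample size of 240 per site". This reproduces: 240 × 1.2 = 288 per site; 288 × 4 = 1,152; 1,152 / 2 = 576 per arm.

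**3. Illustrative count of cancers.** Inputs:

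- n = 576 per arm, with no loss to follow-up (favours the plan).
- Incidence I = 50 to 1,000 per 100,000 woman-years. **Assumption**: the article gives only a six-fold relative risk.
- Observation T = 0.5 or 2 years. Two years is longer than the stated follow-up of the women (favours the plan).
- Screened proportion 15% (control) and 30% (intervention). **Assumption**: Sample size estimation states these for implementation outcomes, with adoption as the example. I apply them to screening completion.
- Screening prevents every cancer at once, and clustering is ignored (both favour the plan).

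Formulas: control mean = n·T·I·(1 − 0.15); intervention mean = n·T·I·(1 − 0.30); expected difference = n·T·I·0.15; Poisson SD of the difference = √(sum of the two means).

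Worked case, I = 200 per 100,000 and T = 2: n·T·I = 576 × 2 × 0.002 = 2.304. The means are 1.958 and 1.613, the difference is 0.346, and the SD is √3.571 = 1.89.

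| I per 100,000 | T (years) | Control | Intervention | Difference | SD | SD / difference | Difference exactly 0 | Wrong sign |
|---|---|---|---|---|---|---|---|---|
| 50 | 0.5 | 0.122 | 0.101 | 0.022 | 0.47 | 22 | 81% | 9% |
| 100 | 0.5 | 0.245 | 0.202 | 0.043 | 0.67 | 15 | 67% | 15% |
| 200 | 2 | 1.96 | 1.61 | 0.35 | 1.89 | 5.5 | 22% | 32% |
| 1,000 | 2 | 9.79 | 8.06 | 1.73 | 4.23 | 2.4 | 9% | 30% |

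The last two columns come from simulated pairs of Poisson counts. When the difference is exactly zero the ICER is undefined. When the sign is wrong, more effective screening appears harmful.

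**4. The same contrast on screening.** Under the same planning rates, extra women screened = 0.15 × 576 = 86.4. The binomial SD, again ignoring clustering, is √[576 × (0.15 × 0.85 + 0.30 × 0.70)] = √194.4 = 13.9. The difference is about 6 times its SD. With four sites, clustering would widen this, but the denominator is a measured quantity of useful size. The article gives no HPV positivity rate, so the difference in women treated cannot be sized in the same way.

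**The case against.** The strongest defence is that cases averted is always an estimated quantity. The article says it will be determined, not counted, and a decision model fed with the trial's screening and treatment results could give a non-zero value with uncertainty unrelated to Poisson cancer counts. A journal article also commonly leaves model structure and horizon to the full protocol or analysis plan. This stands in part. The absence of model details is not itself the defect, and the table above does not describe a modelled result.

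Three stronger readings are tempting, and the document does not support them:

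- **That the denominator must be zero or noise.** This holds only for a count made within the trial, under an assumed incidence and an assumed difference in uptake.
- **That an effect stated for each arm is meaningless.** Each arm could be modelled against no screening, and the paragraph's own general definition of the ICER shows that a between-arm difference is intended. The wording is loose rather than empty.
- **That the trial's main conclusions, or a policy decision resting on this ICER, are compromised.** Outcomes measures makes cost secondary, although the Abstract groups it with the primary outcomes. Neither stated hypothesis concerns cost-effectiveness. The aim of informing policy is stated for the findings in general.

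The defence does not remove the contradiction. The paragraph names one outcome, divides by another, and never says that the second is modelled.

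**Conclusion.** The point holds in this form: the effect measure is inconsistent within one paragraph, and the ICER as written cannot be obtained from the data the trial plans to record. That conclusion rests on the text alone.

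The figures are illustrative. For assumed incidence of 50 to 1,000 per 100,000 woman-years and 6 months to 2 years of observation, a counted difference would be about 0.02 to 1.7 cases, with chance variation from roughly 22 down to 2.4 times as large. If cases averted were modelled, those ratios would not apply.

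The matter should be fixed before the cost-effectiveness analysis is run. It is not critical to the trial: uptake, adoption, sample size and data collection are unaffected, and nothing needed for a sound ICER is lost.

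**What to change.** In Quantitative data analysis, define the trial-based incremental effect as the between-arm difference in (a) women completing screening and (b) screen-positive women treated, each taken over all women enrolled, as the uptake definition already does. Report incremental cost per additional woman screened and per additional woman treated.

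Remove cases averted from the trial-based ICER. If it is wanted, present it as a separate modelled extrapolation, with its comparator, time horizon and progression assumptions stated and varied.

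The change costs wording only, since costs, screening and treatment are already to be collected. The downside is small: cost per woman screened or treated compares less directly with a threshold expressed in health outcomes, and the optional model can address that.

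### The cost-effectiveness rule that compares the ICER with 1 contradicts the plan's own definition of the ICER and runs in the wrong direction

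*Protocol article*

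**What the plan says.** All the relevant text is in the Cost-Effectiveness Analysis item under Quantitative data analysis in the protocol article.

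- **Definition.** The ICER is obtained by "dividing the difference in total costs (incremental cost) by the difference in the chosen measure of health outcome or effect (incremental effect"), and is described as "extra cost per extra unit of health effect". The formula is repeated a little later: "Then ICER = Incremental cost/Incremental effect".
- **Decision rule.** "An ICER of less than 1 indicates that the control group is cost-effective, an ICER greater than 1 suggests the intervention group is cost-effective". The same sentence ends by reading a value equal to 1 as a sign that the arms cost about the same.
- **Effect measure.** The analysis is introduced as one "whose outcome of interest is screening and treatment". The quantity named for the denominator is then "cervical cancer cases averted (incremental effect) for each Arm".

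The abstract lists cost among the primary outcomes. The Outcomes measures section lists it as secondary.

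**The concern.** The rule treats the ICER as a unit-free index with a neutral value of 1, where larger is better for the intervention. The ICER as defined is an amount of money per unit of effect. Its natural reference is what a payer would give for one more unit, and a more effective intervention looks better as the ICER falls.

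A rule that runs the other way can reverse the economic verdict. The implementation support strategies add training and support in the intervention arm, so a costlier intervention arm is plausible. If that arm also raises uptake, the rule would call it cost-effective at almost any price. If it turned out cheaper and better, the rule would favour control.

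The shift in effect measure is a secondary problem. Cost per additional woman screened or treated and cost per cancer case averted are different ratios, and the paragraph does not settle which one the rule applies to.

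**Working it through.** **Inputs.** The formula and the rule are the article's. The article gives no costs, effects, exchange rate or willingness to pay, so every numerical value below is an illustrative assumption.

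**Step 1: the plan's figure.** The cut-off of 1 cannot be derived from the formula. Write ΔC for incremental cost and ΔE for incremental effect (intervention minus control), so ICER = ΔC/ΔE.

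- Equal cost means ΔC = 0, so ICER = 0/ΔE = 0 for any non-zero ΔE. It is not 1.
- ICER = 1 means that ΔC and ΔE are numerically equal. For example, 10/10 = 1, where the arms differ in cost by 10.

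**Step 2: apply the rule in each quadrant.** The comparison is the standard net-benefit criterion: prefer the intervention if λΔE − ΔC > 0, where λ is willingness to pay per unit of effect.

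| Scenario | ΔC | ΔE | ICER | Article's rule | Net-benefit choice |
|---|---|---|---|---|---|
| Costlier, better | 20,000 | 100 | 200 | intervention | intervention only if λ > 200 |
| Very costly, better | 1,000,000 | 1 | 1,000,000 | intervention | intervention only if λ > 1,000,000 |
| Nearly free, better | 50 | 100 | 0.5 | control | intervention if λ > 0.5 |
| Cost-neutral, better | 0 | 10 | 0 | control | intervention at any λ > 0 |
| Cheaper, better | −5,000 | 100 | −50 | control | intervention at any λ > 0 |
| Costlier, worse | 1,000 | −10 | −100 | control | control at any λ > 0 |
| Cheaper, worse | −1,000 | −10 | 100 | intervention | intervention only if λ < 100 |

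The cost-neutral and the cheaper-and-better rows are misjudged at every positive λ. The cheaper-and-better and the costlier-and-worse rows both have negative ICERs. The rule gives them the same verdict, although one intervention is dominant and the other dominated. It is right for the second only because it cannot tell them apart. For a costlier and better intervention, the rule agrees with the net-benefit criterion in favour of the intervention only when the ICER lies between 1 and λ.

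**Step 3: currency.** An ICER of 0.5 restated at an assumed 10 local units per currency unit is 0.5 × 10 = 5. The data are the same, but the verdict moves from control to intervention.

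**Step 4: can another reading rescue the rule?** Subtracting the other way (control minus intervention) changes the sign of both ΔC and ΔE and leaves the ratio unchanged. The stated direction would suit the inverse ratio, effect per unit of cost, when the intervention costs more and does more. The article puts cost in the numerator, and a cut-off of 1 would still depend on the currency.

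**Step 5: effect measure.** Outcomes measures provides binary screening completion, checked within a month of screening, and treatment compliance within 6 months of notification of a positive result. Cancer cases averted is not among the measured outcomes, so it could only be a projection from them.

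**The case against.** The best defence concerns weight and reach. The rule is one interpretive sentence on an outcome that the Outcomes measures section calls secondary. It does not affect randomization, data collection, sample size or the analysis of screening uptake, and it can be corrected before any cost data are analysed. All of that stands, though the abstract's listing of cost as primary leaves its status unsettled. It is no defence that a separate analysis plan may exist. The sentence is a wrong statement, not an omission, and a correct plan elsewhere would simply contradict it.

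Several stronger readings are tempting and should not be adopted:

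- *A reader might infer that the rule approves any costly intervention.* It does not. A costlier and less effective intervention has a negative ICER and goes to control, and a costlier, better one with an ICER below 1 is also rejected.
- *A reader might count the absence of a model for cases averted as a fault.* A condensed article may leave modelling to the full plan. The supported point is narrower: the paragraph names one outcome of interest and uses a different, unmeasured effect.
- *A reader might treat the reference to an incremental effect in each arm as a further error.* It is loose wording. Arm-level quantities can be differenced afterwards, and the same paragraph defines the increment correctly as a difference.
- *A reader might infer that a reversed verdict is likely in this trial.* Nothing in the article shows where the ICER will fall. The examples below 1 and the currency example show the logical fault, not an expected result. The failure more likely to matter in practice is the missing upper limit on what would be called cost-effective.

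**Conclusion.** The concern holds. The decision rule contradicts the definition given in the same paragraph, and nothing elsewhere in the article corrects it. For a more effective intervention the rule runs the wrong way. It has no ceiling above 1 currency unit per unit of effect, and it fails interventions that are nearly free, cost-neutral, or cheaper and better. The cut-off is arbitrary and depends on the currency, and the interpretation of a value equal to 1 is wrong.

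These conclusions follow from the formula alone and need no assumption about actual costs. Only the worked figures are assumed. The size of any error in the trial's own result cannot be stated, because the article gives no cost or effect figures. The consequence is confined to the economic conclusion. The article says that the findings in general should inform national policy, but it does not tie that aim to this rule. The mismatch between screening and treatment and cancer cases averted is real but secondary.

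**What to change.** 1. Delete the comparison of the ICER with 1, including the statement about a value equal to 1.
2. Use observed effects: report incremental cost per additional woman screened and per additional screen-positive woman treated.
3. Report ΔC and ΔE separately and identify dominance from their signs before forming any ratio.
4. Where the intervention is costlier and more effective, call the ICER favourable when it lies below a willingness-to-pay value stated in currency per unit of effect, or report the conclusion over a range of such values. Where it is cheaper and less effective, the comparison reverses, and the text should say so.
5. If cases averted is kept, label it as a separate modelled projection.

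The cost is a change of analysis wording. The cost trackers and the screening and treatment outcomes are already planned, so no new data are needed. Graphical displays such as an acceptability curve are optional and are not required to correct the error.
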